### Statistical analysis methods

2.10

The ITT population will include all randomized participants analyzed according to the group to which they were assigned, regardless of adherence. Missing outcome data will be handled under the MMRM framework. A per-protocol (PP) analysis will also be conducted as a sensitivity analysis, excluding major protocol deviations. All statistical analyses will be performed using SPSS Statistics version 26.0 (IBM Corp., Armonk, NY, USA).

Continuous variables will be described as mean ± standard deviation (SD) or median (interquartile range, IQR), while categorical variables will be presented as frequencies and percentages. Baseline characteristics will be compared between groups using appropriate parametric or non-parametric tests.

The primary outcome (change in MADRS score) will be analyzed using a mixed-effects model for repeated measures (MMRM). The model’s fixed effects will include group, time, and the group-by-time interaction. Baseline MADRS score, the stratification factors (baseline severity and antidepressant use), and the Acupuncture Expectancy Scale score will be included as covariates (37). To assess the robustness of the primary findings and to address potential dilution effects associated with very mild depressive symptoms, a prespecified sensitivity analysis will be conducted excluding participants with baseline MADRS scores in the very mild range (e.g., MADRS < 10). The primary analysis model will be re-run in this restricted sample.

Missing values will be assumed to be missing at random (MAR) within the MMRM framework. Sensitivity analyses will be conducted using multiple imputation and pattern-mixture models. Key secondary outcomes (treatment response and remission rates) will be analyzed using chi-square or Fisher’s exact tests. Logistic regression will be used to adjust these outcomes for covariates, and results will be reported as odds ratios (ORs) with 95% confidence intervals (CIs).

Other continuous outcomes (e.g., MDS-UPDRS III, HADS, PDQ-39, PSQI) will be analyzed using ANCOVA or MMRM. Exploratory mechanistic biomarkers will be analyzed using ANCOVA with a false discovery rate (FDR) correction. These exploratory analyses are intended for hypothesis generation only.

Exploratory associations between biomarker changes (W6–W0) and clinical changes will be examined using multivariable regression (and/or partial correlation) models, adjusting at minimum for baseline biomarker level, baseline outcome severity, age, sex, disease duration, antidepressant use, and changes in levodopa equivalent dose (LED), with multiplicity controlled using false discovery rate (FDR), and these analyses are intended for hypothesis generation rather than confirmatory inference.

All tests will be two-sided, with the significance level set at p < 0.05. De-identified participant data will be stored on a secure, password-protected server accessible only to the research team and will be made available upon reasonable request to the corresponding author after publication.

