#### Waitlist control group

2.7.2

Participants in the waitlist control group will continue their stable, standard medication regimen for the 6-week study period. They will not receive acupuncture or any other study-specific interventions during this time. For ethical reasons, participants in the control group will be offered compensatory acupuncture treatment (using the same protocol as the acupuncture group) after the 6-week intervention period concludes.

To ensure comparability, all participants in both groups must maintain a stable antiparkinsonian medication regimen throughout the study. If any dose adjustments are necessary, they will be assessed by the investigator, documented in the CRF, and converted to the levodopa equivalent dose (LED) (26). No new systemic interventions that could potentially affect depressive symptoms will be permitted during the study. All changes in concomitant medications will be fully documented.

The use and dosage of antidepressant medications will be kept stable whenever possible throughout the 6-week controlled period. “Stable” is defined as no initiation, discontinuation, or dose change within 4 weeks prior to enrollment. During the trial, clinically indicated adjustments will be permitted for safety reasons or symptom worsening. All changes (type, dose, timing, and reason) will be documented and accounted for in the ITT analysis, with sensitivity analyses performed to assess robustness.

To monitor potential contamination during the waitlist period, at each assessment visit participants will be asked using a standardized checklist whether they have received any acupuncture or other non-study interventions for mood or motor symptoms (including acupuncture, electroacupuncture, moxibustion, rTMS, or psychotherapy) since the last visit. Any such use will be recorded as a protocol deviation (type, frequency, timing, and provider) and considered in the per-protocol and sensitivity analyses.

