#### Primary outcome

2.8.1

The primary outcome measure is the change in MADRS total score from baseline (W0) to Week 6 (W6) (27). The MADRS consists of 10 items (total score 0–60) and is highly sensitive to changes in depressive symptoms. Compared to the HAMD, the MADRS places greater emphasis on affective and cognitive dimensions and is less confounded by somatic symptoms (e.g., sleep, appetite, and energy levels) that overlap with PD. This makes it particularly suitable for assessing depressive improvement in patients with PD-D (28).

In addition to analyzing the change as a continuous variable, we will also use the MADRS to calculate the treatment response rate (≥50% reduction) and clinical remission rate (total score ≤10). These outcomes will be interpreted in the context of the minimum clinically important difference (MCID ≈ 2 points) to provide a comprehensive assessment of both statistical and clinical significance (29).

Beyond the primary endpoint at Week 6 (W6), follow-up assessments will be conducted at Weeks 8, 12, and 24 to evaluate the durability and trajectory of treatment effects on depressive symptoms, motor function, sleep quality, and quality of life. These follow-up outcomes are exploratory and will be analyzed descriptively and, where appropriate, using mixed-effects models similar to the primary analysis, without formal adjustment for multiple comparisons.

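### The primary MMRM crosses only group with time, so one baseline-MADRS slope serves every visit; if that slope changes and dropout before Week 6 differs by arm and severity, the Week 6 contrast is slightly biased

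*Protocol article*

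**What the plan says.** Section 2.10 gives the model for change in MADRS: "The model’s fixed effects will include group, time, and the group-by-time interaction". The next sentence reads "Baseline MADRS score, the stratification factors (baseline severity and antidepressant use), and the Acupuncture Expectancy Scale score will be included as covariates (37" (the closing number is a citation). Group is the only term crossed with time.

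The primary time point is Week 6 (section 2.8.1). Table 1 shows Week 6 as the first MADRS after baseline, and section 2.8.1 adds that "follow-up assessments will be conducted at Weeks 8, 12, and 24". Those later outcomes are exploratory and may be analysed "using mixed-effects models similar to the primary analysis". No section lists the visits that enter the primary model.

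On missing data, section 2.10 says: "Missing values will be assumed to be missing at random (MAR) within the MMRM framework". Multiple imputation and pattern-mixture models are planned as sensitivity analyses. Section 2.4 allows for 20% dropout. Sections 2.1 and 2.7.2 offer acupuncture to the control arm once its six weeks are over.

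**The concern.** A baseline main effect in a repeated-measures model assumes that baseline MADRS predicts change equally strongly at every visit. Here treatment changes in both arms after Week 6: the acupuncture course ends in one and is offered in the other. A different slope at later visits is therefore plausible. A shared slope would then be a compromise, and the Week 6 contrast would be adjusted with it.

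With complete data this hardly matters, because randomization stratified on severity keeps the arms' baselines close. It matters if those observed at Week 6 differ in baseline between arms because dropout was selective in different ways. Under MAR, likelihood analysis corrects for such dropout only if the baseline relation at Week 6 is modelled correctly. The quantity at stake is the primary estimate.

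**Working it through.** **Inputs from the protocol article.** Planned difference 2.4 points (2.4); 44 per arm, 88 in total, from 35/(1 − 0.20) = 43.75, rounded up (2.4); baseline MADRS 7 to 34 (2.3.1); severity stratum cut at 19 (2.5); visits W6, W8, W12, W24 (Table 1). The plan gives no figure for the baseline slope, so there is none to reproduce.

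**Assumptions not in the documents.** Baseline mean 20 and SD 6, truncated to 7–34; residual correlation 0.7 per six weeks; slope of change on baseline constant at −0.40, or drifting from W6 to W24 as −0.35 to −0.50 (mild), −0.30 to −0.60 (moderate) or −0.20 to −0.70 (strong). Dropout before W6 was none; 20% unrelated to baseline; 20% related to baseline in controls only (log-odds 0.7 per baseline SD); or 20% in opposite directions (−0.7 acupuncture, +0.7 control). All four visits were modelled, with unstructured covariance. The expectancy score was left out.

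**Formula.** Let D be the difference in mean baseline (acupuncture minus control) among those observed at W6, b6 the true W6 slope and bc the shared slope. The bias in the W6 contrast is approximately (b6 − bc) × D. It is zero if b6 = bc or D = 0.

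**Large-sample check** (3 × 30,000 patients). The simulated bias is the shared-slope estimate minus the estimate with baseline and severity stratum crossed with time, which removes the sampling error common to both.

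| Drift | Dropout before W6 | b6 | bc | D | (b6 − bc) × D | Simulated |
|---|---|---|---|---|---|---|
| None | 20%, opposite | −0.40 | −0.405 | 1.46 | 0.007 | 0.029 − 0.028 = 0.001 |
| Mild | 20%, controls only | −0.35 | −0.441 | 0.76 | 0.069 | 0.101 − 0.035 = 0.066 |
| Mild | 20%, opposite | −0.35 | −0.442 | 1.46 | 0.134 | 0.156 − 0.029 = 0.127 |
| Moderate | 20%, controls only | −0.30 | −0.498 | 0.76 | 0.150 | 0.182 − 0.036 = 0.146 |
| Moderate | 20%, opposite | −0.30 | −0.499 | 1.46 | 0.291 | 0.313 − 0.029 = 0.284 |
| Strong | 20%, opposite | −0.20 | −0.581 | 1.46 | 0.556 | 0.571 − 0.024 = 0.547 |

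With no dropout, or dropout unrelated to arm and baseline, the two models differ by about 0.01 point at most.

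**Trial size** (88 patients, 1,000 replicates, truth −2.4, 20% opposite-direction dropout). The shared-slope model averages −2.42 (constant slope), −2.29 (mild), −2.13 (moderate) and −1.86 (strong). With the interaction it averages −2.42 in all four. As shares of 2.4, the biases are 0.13/2.4 = 5%, 0.29/2.4 = 12% and 0.55/2.4 = 23%. The bias here is toward no effect; reversing either the drift or the dropout pattern reverses its sign.

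**Precision** (empirical SE, shared slope against interaction).
- Mild: 1.265 vs 1.268 without dropout; 1.379 vs 1.389 with it.
- Moderate: 1.291 vs 1.290; 1.409 vs 1.414.
- Strong: 1.310 vs 1.298; 1.485 vs 1.464.

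The shared slope changes the SE by −0.7% to +0.1% under mild to moderate drift and by +0.9% to +1.4% under strong drift. The SE that the model reports rises by up to about 2% under mild to moderate drift (1.213 vs 1.188 at most) and by about 6–7% under strong drift.

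**Sensitivity to the assumptions.** With residual SD 5.5, correlations of 0.6–0.9 and 19% dropout, moderate to strong drift gave 0.06–0.09 points (controls only) and 0.11–0.19 (opposite directions). A further simulation under mild to moderate drift gave 0.05–0.21. Together with the table, this puts mild to moderate drift at roughly 0.05 to 0.3 points.

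**The case against.** The best defence is that this is an article. It says what the fixed effects include, not that the list is closed, and covariate-by-visit terms are often left to an analysis plan. That has some force and keeps the severity low. But the model is written out, one interaction with time is named, and baseline is placed among plain covariates. A programmer following section 2.10 would fit a shared slope.

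The second defence is that the follow-up wording in section 2.8.1 is compatible with separate models, so the primary model might hold only Week 6. Then the point falls away. But Week 6 is the first post-baseline MADRS, and with that visit alone neither time nor group-by-time can be estimated. At least one later visit seems intended. Which ones remains an inference, so a reader should not take it as stated that the slope is held equal over Weeks 6 to 24.

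Third, a reader might infer that the Week 6 contrast is in fact adjusted with a wrong slope. The documents do not support that: they give no slope at any visit, and with a constant slope nothing is wrong. Nor do they support a general loss of precision; the shared-slope model was sometimes marginally more precise.

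Fourth, nothing in the documents shows dropout tied to severity in opposite directions; section 2.4 gives a single 20%. This stands, and that scenario is a stress case. Some difference by arm is plausible, since participants are unblinded (2.6), only one arm has 18 sessions to attend before Week 6 (2.7.1), and poor adherence is a ground for withdrawal (2.3.3). Stratification and the planned missing-data sensitivity analyses help, but they do not by themselves let the slope vary by visit.

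**Conclusion.** The point holds as a conditional one. As written, the primary MMRM uses one baseline-MADRS slope for all its post-baseline visits. The Week 6 estimate is biased only if three things coincide: later visits are in the model, the slope changes across them, and dropout before Week 6 depends on baseline differently by arm. Dropout after Week 6 leaves the Week 6 baselines balanced apart from chance, so it does not create this bias.

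Under mild to moderate assumed drift the bias is about 0.05 to 0.3 points, small beside a standard error of roughly 1.1 to 1.4. The 0.55-point figure needs strong drift together with opposite-direction dropout and should not be read as expected. Drift, dropout pattern and residual correlations are all assumed. There is no material precision loss. Severity: a low-cost improvement.

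**What to change.** In section 2.10, or in the analysis plan if it governs:

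1. List the post-baseline visits in the primary MMRM.
2. Add baseline-MADRS-by-time to the fixed effects, and preferably severity-stratum-by-time, since the stratum is derived from the same score.
3. State that the primary estimate is the Week 6 group difference from that model.
4. Use the same structure in any follow-up MMRM modelled on the primary analysis.

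If only Week 6 is meant to enter, say so and call the analysis ANCOVA at Week 6. In the simulations that gave the same estimates as the interaction model, with almost the same SE (for example 1.415 vs 1.414).

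Cost: with four post-baseline visits, three parameters for baseline-by-time and three more if the stratum is crossed as well. No new data are needed, and the SE stays within about 1% under mild to moderate drift. The change should be fixed before database lock, while the statisticians are still blinded.

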Acupuncture, a safe and widely accepted non-pharmacological therapy, has shown promising potential in the comprehensive management of depression in PD. Evidence from previous studies suggests that acupuncture may influence multiple neurobiological processes relevant to PD-related depression, including neurotransmitter regulation, inflammatory modulation, neurotrophic support, and tryptophan metabolism (16). These mechanisms closely align with the core pathological pathways of PD-related depression, indicating that acupuncture may provide concurrent benefits for both depressive and motor symptoms (17).

However, most existing evidence comes from exploratory studies with small sample sizes, single-center designs, and considerable methodological heterogeneity. As a result, high-quality data that systematically integrate clinical outcomes with objective biological markers remain scarce (18).

Despite these encouraging findings, several key uncertainties remain. Prior studies are often limited by exploratory designs, restricting the precision and interpretability of effect estimates. In addition, most research has relied predominantly on symptom-based outcomes, with limited integration of objective biological markers, leaving it unclear whether observed clinical improvements reflect modulation of underlying neurobiological pathways. Finally, although depression and motor dysfunction in Parkinson’s disease interact bidirectionally, it remains uncertain whether acupuncture is associated with concurrent improvements across both affective and motor domains within the same clinical framework.

Accordingly, we designed a prospective, evaluator-blinded randomized controlled trial to evaluate the efficacy and safety of acupuncture as an adjunct to stable standard pharmacotherapy in patients with Parkinson’s disease and comorbid depression. This study integrates serum biomarkers—including inflammatory cytokines, brain-derived neurotrophic factor (BDNF), and the kynurenine/tryptophan (KYN/TRP) ratio—with clinical outcome measures, enabling an exploratory assessment of whether acupuncture is associated with coordinated improvements in depressive and motor symptoms through shared neuro–immune–endocrine pathways.

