### Sample size

2.4

The sample size was estimated using an Analysis of Covariance (ANCOVA) for the primary outcome: the change in MADRS score from baseline (W0) to Week 6 (W6). Based on prior exploratory research (21) and the conversion formula by Leucht et al. (22), the pre-specified between-group difference (Δ) was set at approximately 2.4 points. An assumed common standard deviation (SD) of approximately 6.0 points for MADRS change scores was adopted, which is consistent with reported variability in previous studies of depression in Parkinson’s disease. This corresponds to a standardized effect size (Cohen’s d) of approximately 0.40. Statistical parameters were set at α = 0.05 (two-tailed) and a power of 1-β = 80%. The calculation, performed using G*Power 3.1 (23), indicated that 35 completers per group are required. To account for a potential 20% dropout rate, we plan to recruit 44 participants per group, resulting in a total sample size of 88. Although the primary analysis will use a mixed-effects model for repeated measures (MMRM), the sample size was estimated using an ANCOVA framework as a conservative approximation for the baseline-adjusted between-group comparison at Week 6.

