#### Key secondary outcomes

2.8.2

To supplement the primary outcome, the key secondary outcome is the change in the Movement Disorder Society Unified Parkinson’s Disease Rating Scale Part III (MDS-UPDRS III) score (30).

The MDS-UPDRS III is an internationally recognized tool for assessing motor function in PD. It consists of 33 items with a total score ranging from 0 to 132, where higher scores indicate more severe motor impairment. In this study, it will be used to evaluate motor function improvement and perform correlation analysis with changes in MADRS scores.

All assessments will be conducted while participants are in their “ON” medication state (60–90 minutes after oral levodopa administration), and the interval since the last dose will be recorded.

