For our mechanistic exploration, we selected three categories of serum biomarkers: inflammatory cytokines (IL-6, TNF-α, hs-CRP), BDNF, and the KYN/TRP ratio. These were chosen to map onto neuroinflammation, neuroplasticity, and the tryptophan metabolic pathway, respectively. Elevated inflammatory factors can exacerbate emotional and motor impairments by disrupting monoamine function and accelerating neuronal degeneration (46). Reduced BDNF limits emotional regulation and motor learning capacity (47).

Furthermore, a KYN/TRP imbalance not only reduces serotonin synthesis substrates but also promotes the accumulation of neurotoxic metabolites, such as quinolinic acid. This process bidirectionally drives both depressive and motor impairments (48). Therefore, these biomarkers serve as pivotal links between depression and motor impairment and may also function as objective measures of acupuncture’s effects. If acupuncture can simultaneously alleviate clinical symptoms and modulate these biological pathways, this would provide preliminary, hypothesis-generating evidence that acupuncture may attenuate the bidirectional interplay between emotional and motor symptoms (49).

The strengths of this study include its randomized controlled design, stratified randomization based on baseline depression severity and antidepressant use, assessor blinding, and the integration of multidimensional clinical outcomes with mechanistic biomarkers reflecting neuroinflammation, neuroplasticity, and tryptophan metabolism. These features allow for a comprehensive evaluation of the clinical effectiveness of acupuncture and its potential biological correlates in Parkinson’s disease with depression.

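### The minimum adjustment set for the exploratory biomarker-change versus clinical-change models leaves out randomised group

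*Protocol article*

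**What the plan says.** Section 2.10 (Statistical analysis methods) states: "Exploratory associations between biomarker changes (W6–W0) and clinical changes will be examined using multivariable regression (and/or partial correlation) models". The covariates are then fixed as a floor: "adjusting at minimum for baseline biomarker level, baseline outcome severity, age, sex, disease duration, antidepressant use, and changes in levodopa equivalent dose (LED"). That makes seven terms, and randomised group is not one of them. The same sentence sets the status of the analysis: "with multiplicity controlled using false discovery rate (FDR), and these analyses are intended for hypothesis generation rather than confirmatory inference".

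The primary model in the same section does name the arm: "The model’s fixed effects will include group, time, and the group-by-time interaction".

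Section 2.8.2 (Key secondary outcomes) adds that the MDS-UPDRS III will be used to "perform correlation analysis with changes in MADRS scores", with no model or covariates given. The Introduction describes the purpose of combining biomarkers with clinical measures as "enabling an exploratory assessment of whether acupuncture is associated with coordinated improvements in depressive and motor symptoms through shared neuro–immune–endocrine pathways".

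The article does not say whether the change-on-change models pool the two arms or are run within each arm.

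**The concern.** Randomised group is a potential common cause of both changes. Suppose acupuncture, or the expectation that goes with an unblinded treatment compared with a waitlist, lowers MADRS, and separately shifts a marker such as BDNF. Patients in the acupuncture arm then tend to have larger values of both changes, and patients in the control arm smaller values of both. Pooled, the two changes correlate even if, within either arm, knowing one says nothing about the other. None of the seven listed covariates carries the arm, so none of them removes this.

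What is at stake is interpretation. A pooled association of this kind would look like a biological correlate of clinical improvement, while adding nothing to the two separate group comparisons. If both effects go the way the trial hypothesises, the artefact goes that way too. False discovery rate control limits chance findings across several tests. It does not correct p-values that are already distorted by an omitted common cause.

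**Working it through.** **Inputs from the article (Sample size, 2.4; Study design, 2.1).** "the pre-specified between-group difference (Δ) was set at approximately 2.4 points"; SD of MADRS change 6.0; 35 completers per group; 20% dropout; 1:1 allocation.

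- Standardised clinical effect: 2.4 / 6.0 = 0.40, as stated.
- Recruitment: 35 / 0.80 = 43.75, rounded up to 44 per group, 88 in total, as stated.
- Data set sizes used below: 2 × 35 = 70 and 2 × 44 = 88.

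The article gives no sample size or power for the association analysis, so there is no stated figure to reproduce for it. (A plain two-sample calculation at d = 0.40, two-sided 5% and 80% power gives 99 per group, not 35. That is a separate matter. Here 35 serves only as the size of the data set.)

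**Assumption.** The article gives no treatment effect on any biomarker, so that effect is varied.

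**Induced correlation.** Let d_c and d_b be the group effects on clinical and biomarker change in within-arm SD units, signed so that the hypothesised direction is positive, with zero within-arm correlation. With half the patients in each arm, the pooled covariance is ½ × ½ × d_c × d_b, and the pooled variances are 1 + d_c²/4 and 1 + d_b²/4. Hence

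r = (d_c d_b / 4) / √[(1 + d_c²/4)(1 + d_b²/4)].

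- d_c = 0.40, d_b = 0.2: 0.02 / √(1.04 × 1.01) = 0.020
- d_c = 0.40, d_b = 0.8: 0.08 / √(1.04 × 1.16) = 0.073
- d_c = d_b = 0.8: 0.16 / 1.16 = 0.138
- d_c = d_b = 1.0: 0.25 / 1.25 = 0.200

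**False-positive rate.** The simulation used 6,000 runs per setting, zero within-arm link, seven covariates in the model (generated independently of both changes), and a two-sided test at 5% for a single association before any false discovery rate step. The Monte Carlo standard error near 5% is √(0.05 × 0.95 / 6000), about 0.3 percentage points.

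| MADRS effect (SD) | Biomarker effect (SD, assumed) | Induced r | Group omitted, N = 70 / 88 | Group included, N = 70 / 88 |
|---|---|---|---|---|
| 0.40 | 0.2 | 0.020 | 5.6% / 5.3% | 4.9% / 4.8% |
| 0.40 | 0.4 | 0.038 | 5.6% / 6.7% | 4.6% / 5.8% |
| 0.40 | 0.5 | 0.048 | 7.0% / 7.8% | 5.3% / 5.4% |
| 0.40 | 0.8 | 0.073 | 8.7% / 10.2% | 5.1% / 5.1% |
| 0.40 | 1.2 | 0.101 | 12.6% / 14.9% | 4.8% / 5.0% |
| 0.67 | 0.67 | 0.101 | 12.8% / 14.7% | 5.1% / 4.4% |
| 0.8 | 0.8 | 0.138 | 19.4% / 23.2% | 4.7% / 4.6% |
| 1.0 | 1.0 | 0.200 | 34.8% / 44.2% | 5.0% / 5.1% |

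With group in the model the rate stays close to 5% throughout. If the treatment does not move the biomarker at all, omitting group does no harm (5.0% / 4.5%).

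**The case against.** The strongest reply has four parts.

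- **The list is a floor.** Its wording allows further covariates, and pooling is implied by silence rather than stated. A condensed article may leave the full model to a longer document. This stands in part: group is not forbidden. But the authors chose to publish a specific list, down to the change in levodopa equivalent dose, and an analysis without group complies with it. The arm is the one term whose omission creates a known bias, so it belongs in the floor.
- **The analysis is exploratory and controlled for multiplicity.** This stands as a limit on the consequences. It does not answer the bias itself. It does mean that the rates above, which are for one test at an unadjusted 5%, are not the error rates of the full planned procedure.
- **The correlation in section 2.8.2 has no specified model.** This stands. No error can be charged there, and the sensible step is to carry the same adjustment across.
- **The effect is small at the planned size.** This stands, and the point is worded accordingly.

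Two stronger readings are tempting. A reader might infer that any treatment that moves both variables will produce a spurious finding. That is true of the expected correlation, but at d = 0.40 a significant result would be only slightly more frequent than chance. A reader might also infer that the paper's mechanistic message rests on these regressions, citing the Discussion's phrase "these biomarkers serve as pivotal links between depression and motor impairment". That phrase is background rationale for choosing the markers. The Discussion's own conditional claim concerns treatment effects on symptoms and on biomarkers, which the primary model and the biomarker ANCOVA address directly, and it is called preliminary.

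**Conclusion.** The point holds in a limited form. The minimum adjustment set omits randomised group, and the article does not supply it elsewhere or confine the models to one arm. If the arms are pooled under that list, part of any observed association may be no more than the difference between arms.

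At the planned MADRS effect of 0.40 SD and assumed biomarker effects of 0.2 to 0.8 SD, the induced correlation is about 0.02 to 0.07, and the nominal 5% false-positive rate becomes about 5% to 10%. Rates of about 20% or more require both effects to be about 0.8 SD or larger, which is twice the planned clinical effect. These figures assume no within-arm correlation, 70 to 88 patients and covariates unrelated to either change. The biomarker effects are not taken from the article.

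The consequence is confined to the exploratory mechanistic interpretation. The primary comparison includes group and is unaffected. The correction is worth making because it is nearly free and removes a bias that would favour the hypothesis.

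**What to change.** In section 2.10, add randomised group to the minimum adjustment set for all biomarker-change versus clinical-change regressions and partial correlations. In section 2.8.2, state that the correlation between MADRS change and MDS-UPDRS III change uses the same adjustment, group included.

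Within-arm estimates may be shown as a descriptive check. They are optional: with about 35 completers per arm and at least seven covariates they would be imprecise.

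The cost is one covariate and one degree of freedom per model, with no new data or visits. Adding group removes the part of the association that comes from arm differences. What remains is still an observational within-arm association and should be reported as such.
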